The secondary outcomes will be assessed by the scores of the following validated questionnaires: 1) King’s Health Questionnaire (KHQ); 2) Urinary Distress Inventory (UDI-6); 3) Pelvic Floor Impact Questionnaire (PFIQ-7); 4) Patient Global Impression of Improvement (PGI-I).

Sample Size

Power analysis methodology represents a design, with two levels of the between-subject factor of two study groups and four levels of the within-subjects factor of time. A repeated measures ANOVA power analysis was conducted. The effect size for this calculation used the ratio of the standard deviation of the effects for a particular factor or interaction and the standard deviation of within-subject effects. The power analysis was conducted for a single, two-group between-subjects factor, and a single within-subjects factor assessed over four time points. For this design, 50 participants (25 per group) achieve a power of 0.80 for the within-subjects main effect at an effect size of 0.25; a power of 0.80 for the between-subjects main effect at an effect size of 0.32 and a power of 0.80 for the interaction effect at an effect size of 0.25.

Statistical analysis

Comparison of data between the compared groups in both phases will be based on the intention-to-treat principle. Randomisation will be done for all women. Later dropouts and those not adhering to protocol will be excluded. The normality assumption will be evaluated using the Kolmogorov-Smirnov test. Student’s t-tests will be computed for the comparison of a continuous variable between two groups when the distribution is normal and the Mann-Whitney test when the distribution is not normal. Paired t-tests and Wilcoxon signed rank tests will be used for pre and post comparisons. 

For the comparison of proportions between the two study groups, Chi-square and Fisher’s exact tests will be used. Repeated measurements ANOVA will be performed to evaluate the changes observed between control and intervention group over the follow-up period. Additionally, three sensitivity analyses will be performed: per-protocol analysis, robustness of trial accounting for missing data, and adjusting for baseline covariates. Per-protocol analysis will include women who will complete the therapeutic protocol.

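### The analysis is labelled intention-to-treat, but dropouts and non-adherers are removed, so the main comparison becomes a completer analysis that the per-protocol sensitivity analysis largely repeats

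*Protocol article*

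**What the plan says.** All the relevant text is in the Statistical analysis section of the protocol article (Materials and methods). Three consecutive sentences fix the analysis population:

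1. "Comparison of data between the compared groups in both phases will be based on the intention-to-treat principle"
2. "Randomisation will be done for all women"
3. "Later dropouts and those not adhering to protocol will be excluded"

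Further on, the section adds: "three sensitivity analyses will be performed: per-protocol analysis, robustness of trial accounting for missing data, and adjusting for baseline covariates". The per-protocol set is then defined: "Per-protocol analysis will include women who will complete the therapeutic protocol".

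The third sentence carries no qualifier. Nothing else in the article restricts it to a secondary population or defines a modified intention-to-treat set. The Sample Size section bases its power on 50 women, 25 per group, and states no allowance for loss.

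**The concern.** Intention-to-treat means that women are compared as randomised, whatever they do afterwards. Removing those who drop out or do not adhere is the opposite rule. If the exclusion is applied, three things follow.

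- **The comparison loses the protection of randomisation.** Whether a woman leaves or adheres is decided after allocation. The arms receive different exposures (40 W against 0.5 W, Table 3), and the primary outcomes are the OAB-q and a voiding diary, both completed by the patient. Reasons for leaving could differ by arm and be related to outcome, so a difference between arms could reflect who was removed.
- **Two of the three sensitivity analyses lose their purpose.** The per-protocol analysis would use nearly the same women as the main one, and most women with missing follow-up would already be gone before the missing-data analysis starts.
- **The result would be misdescribed.** Readers would see an intention-to-treat label on a completer analysis.

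**Working it through.** **Step 1. The rules side by side (no arithmetic needed).**

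| Rule | Who is analysed |
|---|---|
| Intention-to-treat sentence | every randomised woman, as allocated |
| Exclusion sentence | randomised women, minus dropouts, minus non-adherers |
| Per-protocol definition | women who complete the therapeutic protocol |

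Row 1 and row 2 agree only if nobody drops out or deviates. Rows 2 and 3 are essentially the same set. They could differ by a few women, because neither adherence nor completion is given an operational rule. For example, a woman who has all three sessions but departs from the protocol in another way fails row 2 and meets row 3.

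**Step 2. The plan's own power figure.** Inputs from the Sample Size section: N = 50, 2 groups, m = 4 time points, power 0.80 at effect size f = 0.32 (between subjects) and f = 0.25 (within subjects and interaction). Two-sided 0.05 is from the Statistical analysis section. The article gives neither the correlation between visits (ρ) nor the sphericity factor (ε); I assume ρ = 0.5 and the lower bound ε = 1/3.

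- Between: λ = f²·N·m / (1 + (m−1)ρ) = 0.1024 × 200 / 2.5 = 8.192, on 1 and 48 df. Power is 0.801.
- Interaction: λ = ε·f²·N·m / (1−ρ) = (1/3) × 0.0625 × 200 / 0.5 = 8.333, on 1 and 48 df. Power is 0.807.

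So the stated 0.80 can be reproduced and is not in error, but it belongs to 50 analysed women. (With ε = 1 the interaction power would be 0.992, so that match depends on the assumed ε.) Under the same assumptions, with fewer women analysed:

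| Women analysed | Between | Interaction |
|---|---|---|
| 50 | 0.801 | 0.807 |
| 46 | 0.766 | 0.773 |
| 44 | 0.746 | 0.754 |
| 40 (20% loss) | 0.704 | 0.711 |
| 36 | 0.655 | 0.663 |

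**Step 3. Bias by formula.** Assume no true effect, exclusions in one arm only, a single end-point comparison, and excluded women averaging s SD worse than the arm mean. If a fraction d is removed, the mean of those who remain shifts by d·s/(1−d). For d = 0.20, 20 women are compared with 25:

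- s = 0.5: 0.20 × 0.5 / 0.80 = 0.125 SD. s = 1.0: 0.25 SD.
- Standard error = √(1/25 + 1/20) = 0.30 SD.
- Two-sided error = P(Z > 1.96 − shift/SE) + P(Z < −1.96 − shift/SE). This is 7.0% at 0.125/0.30 and 13.3% at 0.25/0.30.

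At 12% removed (22 against 25) the corresponding error is 5.6% to 7.5%.

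**Step 4. Bias by simulation.** Assume 25 per arm, no true effect, change score with SD 1, and a leaving score equal to the change plus noise; the lowest scorers leave, and a t-test is run on those who remain. Ranges cover repeated runs.

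| Loss, arm 1 v arm 2 | Noise SD | Bias (SD) | False positives |
|---|---|---|---|
| 20% v 4% | 1 | 0.18 | 10–11% |
| 12% v 4% | 1 | 0.10 | 7–7.5% |
| 8% v 4% | 1 | 0.05 | about 6% |
| 20% v 20% | 1 | about 0 | 6–7% |
| 20% v 4% | 3 (weaker link to outcome) | 0.08 | about 6% |

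Part of the excess comes from removing a fixed number of women per arm, which is why equal loss still shows 6–7% without bias. When each woman leaves independently with a given probability, the rates are 5.0% (20% v 20%), 9.5% (20% v 4%) and 6.2% (12% v 4%).

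**The case against.** The strongest reply is that the exclusion sentence was meant to describe only the per-protocol set. The article lists a per-protocol analysis as additional and plans one for missing data; both presuppose a main set wider than completers. That may well be the intention. However, the sentence directly follows the intention-to-treat statement, comes before the per-protocol analysis is introduced, and is unqualified. On this reading too, the text needs correcting. An unshown analysis plan might settle the matter, but it would not remove a wrong rule from the published protocol.

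Three narrower points stand:

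- The main and per-protocol sets overlap almost entirely, but are not defined identically.
- The article documents neither a dropout rate nor any difference in dropout between arms. It describes the laser as well tolerated, follow-up is three months, and patients and investigators are blinded. Differential loss is a possibility, not something shown, and modest loss or a weak link to outcome gives little inflation.
- The mixed model is named in the article for adjustment for confounding, while repeated-measures ANOVA is assigned to the group comparison over time. Making the mixed model the main analysis changes its role and should be stated as such.

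**Conclusion.** The concern holds. The article states two incompatible rules for its main population, and the one with operational content turns the main analysis into a completer analysis under an intention-to-treat label. This follows from the text alone.

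The consequence depends on how many women leave, how unevenly, and how strongly leaving is tied to outcome, none of which the article gives. Over the uneven-loss scenarios in which 12% or 20% of the more affected arm is removed, bias runs from about 0.07 to 0.25 SD (the lower end is 0.12 × 0.5 / 0.88) and the nominal 5% error becomes roughly 6% to 13%. Equal loss gives no bias under the model used. Separately, analysing 40 women rather than 50 lowers the planned power from about 0.80 to about 0.70, given the assumed ρ and ε. The point must be fixed before analysis.

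**What to change.** - **Population.** Delete the exclusion sentence or confine it explicitly to the per-protocol set. State that the main analysis includes every randomised woman in her allocated arm, regardless of sessions attended or adherence.
- **Model.** Use all available visits in the mixed linear model the article already names, and say that this is now the main analysis. Deleting the sentence is not enough if repeated-measures ANOVA stays primary, because it normally drops any woman with a missing visit and so brings the completer analysis back. The mixed model relies on data missing at random; the planned missing-data sensitivity analysis should examine departures from that.
- **Data.** Continue to collect questionnaires and diaries from women who miss sessions or stop mirabegron.
- **Per-protocol set.** Keep it as a sensitivity analysis, with one operational definition of completion and adherence.

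**Cost.** A wording change, plus follow-up of self-completed forms; no extra patients. Since analysis was expected in early 2024, data from women who have already left may be unobtainable; the population and model can still be corrected. By contrast, keeping the exclusions and still analysing 50 women would require randomising 56, 63 or 72 at 10%, 20% or 30% loss (50/0.9, 50/0.8, 50/0.7, rounded up), and the bias would remain.

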If the woman is eligible to participate, she will be asked to complete a three-day micturition diary for the previous week and fill in the Overactive Bladder Questionnaire (OABq), King’s Health Questionnaire (KHQ), Urinary Distress Inventory (UDI-6), and Pelvic Floor Impact Questionnaire (PFIQ) before every session. The Patient Global Impression of Improvement (PGI-I) questionnaire will be filled in only one time at the end of the study. All information will be evaluated in order to assess the improvement of frequency in micturition, urgent episodes and urinary incontinence, the impact of OAB symptoms on their quality of life, such as daily activities, relationships, feelings, botherness, personal and physical limitations and finally will be evaluated the patient’s impression of improvement one month after the last session in both groups.

The patients enrolled in the study must fulfill the following criteria shown in Table 1. Patients who cannot participate in the study are shown in Table 2.

**Table 1 TAB1:** Inclusion criteria FSH: follicle stimulating hormone

Inclusion Criteria
Postmenopausal women (≥12 months of amenorrhea or FSH ≥30-40 after total hysterectomy)
Overactive bladder syndrome: ≥three months symptoms of urgency, with or without urinary incontinence, and ≥eight episodes/24h
At least three episodes of urgent urination (3rd-4th grade) under PPiUS (patient perception intensity of urgency scale) during a three-day urination calendar, with or without urinary incontinence

**Table 2 TAB2:** Exclusion Criteria

Exclusion Criteria
Genital prolapse >2nd degree according to the Pelvic Organ Prolapse classification system
Voiding residue volume >200 ml
Obstruction bladder
Use of vaginal estrogen in the last month
Use of drugs for urinary incontinence
Use of psychiatric drugs
Urinary or genital infection
Kidney or liver disease
Cardiac conduction or rate disorders
Arterial hypertension unregulated
Neurological diseases and diabetic neuropathy
Myasthenia
Cancer
Previous radio-chemotherapy

Randomization

Eligible patients are randomized 1:1 using a computer-generated randomization scheme, to receive active laser therapy or placebo, once monthly for three months.

Interventions

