Adjustment for confounding factors will be performed using mixed linear regression models that account for multiple measurements per individual obtained at different time points. All reported p values will be two-tailed and statistical significance is set at p<0.05.

Adverse effects

Patients with severe or uncontrolled hypertension should not take mirabegron and will be excluded from the study. While clinical trials have not demonstrated significant increases in blood pressure compared with placebo [12], patients can develop hypertension. Blood pressure will be monitored, and in case of any adverse event, blood pressure medications could be adjusted according to the primary care clinician's suggestion.

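### A normality pre-test of unstated form picks between t-test and Mann-Whitney, has low power for moderate skew at 25 per arm, and leaves the ANOVA on which the trial is powered ungated

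*Protocol article*

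**What the plan says.** All of this stands in the protocol article, Materials and methods.

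- Statistical analysis: "The normality assumption will be evaluated using the Kolmogorov-Smirnov test". A two-group comparison of a continuous variable then uses Student's t-test if the distribution is judged normal, "and the Mann-Whitney test when the distribution is not normal".
- The same section adds, with no such condition, "Repeated measurements ANOVA will be performed to evaluate the changes observed" between the arms during follow-up. It also lists baseline adjustment as a sensitivity analysis and mixed linear models for confounder adjustment.
- The significance rule is common to all tests: "All reported p values will be two-tailed and statistical significance is set at p<0.05".
- Sample Size rests only on the repeated-measures ANOVA with two groups and four time points: "50 participants (25 per group) achieve a power of 0.80 for the within-subjects main effect at an effect size of 0.25". It claims the same power for the group effect at f = 0.32 and for the group-by-time interaction at f = 0.25.
- Primary Outcomes names the OAB-q score and three measures from a three-day diary: micturition frequency, urgency and incontinence.

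The text does not say which version of the Kolmogorov-Smirnov test is meant, at what level it is run, or whether it is applied to each arm, to pooled data or to changes. No between-group test is named as the primary one.

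**The concern.** The t-test compares means and the Mann-Whitney test compares ranks. They test different hypotheses and lead to different estimates, so a rule that chooses between them from the trial's own data leaves both open until the data are seen. The choice could also fall differently for different outcomes or visits, although the article does not say that it is made visit by visit.

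The gate is also inconsistent with the rest of the plan. A variable found too non-normal for a t-test would still be analysed by repeated-measures ANOVA, which rests on the same kind of distributional assumption. Two between-group p values for one outcome can then differ, with nothing to say which one counts.

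Skew is plausible here. Table 1 admits women with or without incontinence, so many incontinence counts may be zero, and it sets entry floors for frequency and urgency that cut off the lower tail at baseline.

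**Working it through.** **Inputs from the article.** 25 per arm, 1:1 ("Eligible patients are randomized 1:1 using a computer-generated randomization scheme"), four time points, two-sided 0.05, stated power 0.80 at effect sizes f of 0.32 (between), 0.25 (within) and 0.25 (interaction).

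**Assumed, because the article gives no figure.** The shape of the diary counts, the form of the pre-test, the correlation between visits (rho) and the sphericity factor (eps).

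**1. The plan's own power figure.** Noncentral F with N = 50 and m = 4.

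- Between groups: lambda = f² × N × m / (1 + (m − 1) × rho) = 0.1024 × 200 / 2.5 = 8.19 at rho = 0.5. With df 1 and 48, power is 0.801.
- Within and interaction: lambda = eps × f² × N × m / (1 − rho) = (1/3) × 0.0625 × 200 / 0.5 = 8.33. With df 1 and 48, power is 0.807.

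All three stated values reproduce with rho = 0.5 and eps = 1/3. (With eps = 1, the within and interaction power would be 0.992.) The sample size is thus an ANOVA calculation, and neither of the two gated tests enters it.

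**2. How often the pre-test flags one arm of 25.** 20,000 simulated trials per distribution. D is the largest gap between the empirical distribution and the normal one fitted with the sample mean and SD. It is compared with 0.173 (Lilliefors) or 0.264 (uncorrected). The last two columns give the chance that Mann-Whitney is used if either arm is flagged, which is 1 − (1 − p)² apart from simulation error. For example, 1 − 0.776² = 0.40 at skew 1.0, against 0.39 simulated.

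| Assumed shape | One arm, corrected | One arm, uncorrected | Mann-Whitney used, corrected | Mann-Whitney used, uncorrected |
|---|---|---|---|---|
| Frequency-like count, skew 0.6 | 12% | 0.1% | 22% | 0.2% |
| Gamma, skew 0.7 | 13% | 0.1% | 25% | 0.3% |
| Gamma, skew 1.0 | 22% | 0.3% | 39% | 0.7% |
| Gamma or count, skew 1.4 | 40–44% | 1.5–2% | 64–68% | 3–4% |
| Exponential, skew 2.0 | 70% | 7% | 91% | 14% |
| Zero-heavy count | 99.5% | 63% | 100% | 86% |

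The unstated version matters a great deal. At skew 2.0 the same data lead to Mann-Whitney in 91% or in 14% of trials. The unit matters too: testing the pooled 50 values at skew 2.0 flags 96% (corrected) or 38% (uncorrected).

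**3. What the gate does to the test result.** With no true effect, the two-stage rule (either arm) rejects in 0.048–0.053 of trials (corrected) and 0.047–0.056 (uncorrected). The t-test alone gives 0.041–0.051 and Mann-Whitney alone 0.045–0.050. With a true effect (a shift of 0.8 SD or a proportional reduction), the two tests disagree on significance in about 6–11% of trials at skew 0.6–1.4, and in about 1–18% over all shapes tried.

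**4. What unused baseline data cost.** Assume normal data, a true effect of 0.7 SD and baseline correlation r of 0.4 to 0.6. The noncentrality is d × √(25/2), where d is the effect over the SD that applies.

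- Follow-up values, t-test: d = 0.7, noncentrality 2.47, power 0.68.
- Change scores: d = 0.7 / √(2(1 − r)) = 0.64 to 0.78, power 0.60 to 0.77.
- Baseline as covariate: d = 0.7 / √(1 − r²) = 0.76 to 0.875, power 0.75 to 0.86.

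A simulation with the same effect and correlations gave 0.66–0.69, 0.61–0.77 and 0.76–0.84.

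**The case against.** The strongest reply is that the gate does little harm. The article never calls the t-test and Mann-Whitney pair primary. It assigns the between-group change over follow-up to the ANOVA and powers the trial on that. When the pre-test misses skew, the t-test that follows still holds its level. The corrected version works well for the most skewed data. The version and unit of a pre-test are also details that a full protocol or analysis plan may supply. Baseline is not ignored overall: the ANOVA's four levels match the visits at months 0 to 3, baseline adjustment is a named sensitivity analysis, and mixed models are planned.

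Most of this stands, and it rules out a stronger reading. A reader might infer that the pre-test barely detects skew at all and turns the primary test of the diary counts into something close to a coin toss. The documents and the figures do not support that:

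- The gated pair is not designated primary.
- Detection is 70% at skew 2.0 and 99.5% for zero-heavy counts with the correction.
- The choice of test is near even only in some settings, such as skew of about 1.0 to 1.4 with the correction. For zero-heavy counts it goes to Mann-Whitney in 86 to 100% of trials if either arm decides.
- The result of the test is not left to chance. Type I error stays near 5%, and the two tests agree in at least about 82% of simulated trials.

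The reply does not remove the rule itself. Choosing the test from the data is what the article states, not something it leaves out, and a fuller specification of the pre-test would keep that dependence. Nor does it explain why a variable that fails the gate is still fit for ANOVA.

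**Conclusion.** The point holds in a limited form. The plan fixes a data-dependent choice between two tests of different hypotheses. The pre-test that makes the choice has low power for moderate skew at 25 per arm: about 12 to 44% per arm with the Lilliefors correction and 3% or less without, at skew 0.6 to 1.4. It also has no bearing on the ANOVA that carries the sample size, so differing between-group p values for one outcome are possible.

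The damage is to pre-specification and efficiency, not to the error rate. On the assumptions in step 4, the t-test on follow-up values has power of about 0.68, against 0.75 to 0.86 with baseline as covariate. This loss applies to the t-test and Mann-Whitney on follow-up values. If changes are what is tested, baseline does enter, though less efficiently.

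The detection, disagreement and power figures rest on assumed shapes, effects and correlations. Since the article assumes no dropout, 25 per arm is the largest number available, and detection would be no better with fewer.

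**What to change.** Delete the normality gate. Name one between-group analysis in advance for the primary outcomes: the linear mixed model already planned under Statistical analysis, with the baseline value of the outcome as covariate and a group-by-visit term. State which contrast from that model is the one to be read.

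For incontinence counts with many zeros, fix one method in advance, for example rank ANCOVA or a negative binomial model. The calculations above do not compare these two at 25 per arm, so either is acceptable provided it is chosen before the data are seen. Keep Mann-Whitney only as a sensitivity check labelled as such.

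The cost is a change of analysis wording and slightly more modelling work. No new data are needed, since baseline values are already collected at month 0. The change should be made before unblinding.

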## Abstract

Introduction: This is a presentation of a study protocol in order to evaluate whether the application of CO2 laser can additionally benefit the improvement of the symptoms of overactive bladder in postmenopausal women who have just started mirabegron as a treatment.

Materials and methods: This is a study protocol of a randomized double-blind placebo-controlled trial. A total of 50 menopausal women will participate in the study. All patients will start treatment with mirabegron 50 mg and will be randomized into two groups. Women in group A (control) will undergo CO2 laser treatments while those in group B (placebo group) will receive placebo CO2 laser treatments. In total, three monthly sessions will be held in both groups. The monitoring and evaluation of the results will be carried out by completing a three-day urination diary, as well as by completing the Female Lower Urinary Tract Symptoms, Overactive Bladder Questionnaire, King’s Health Questionnaire, Urinary Distress Inventory, Pelvic Floor Impact Questionnaire, Patient Global Impression of Improvement, before each session and a month after the last one. Differences between groups will be assessed at baseline and every month following the three laser therapies.

Results: This is an ongoing study protocol, and we are expecting the analysis of the results in 2024.

Conclusions: The use of laser CO2 in postmenopausal women with overactive bladder syndrome may be a well-tolerated alternative treatment. The goal of our study is to evaluate the efficacy of laser treatment in combination with b3-adrenoreceptor agonist therapy.

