All participants will receive treatment with mirabegron 50mg and they will equally be divided in active or placebo laser therapy. Fractional CO2 laser (SmartXide2 V2LR, Monalisa Touch, DEKA, Florence, Italy) will be applied at monthly intervals in both groups. The parameters of the machine can be changed manually and are presented in Table 3.

**Table 3 TAB3:** The machine laser parameters that are going to be used in each session of each group.

Laser Group	Placebo Group
Microablative fractional CO2 laser therapy at monthly intervals	Placebo CO2 laser therapies at monthly intervals
Power: 40 watts	Power: 0.5 watts
Dwell time: 1000μs	Dwell time: 1000μs
Spacing 1000 μm	Spacing 1000 μm
Depth: SmartStak parameter 3	Dwell time: 1000μs
D-pulse mode	Smart-pulse mode

Both groups will receive a total of three sessions. The technique of the vaginal therapy will be identical for both groups. The basic difference in parameters of these two groups are in power and emission mode.

Blinding

The investigator, study site personnel and patients will all be blinded to treatment. An unblinded nurse will be responsible for programming the laser parameters, before the doctor and patient enter the examination room. The screen of the laser system will be covered to ensure proper blinding. Although in the placebo group the power of 0.5 watts and smart pulse emission mode will not allow energy submission to the vaginal tissue, the identical laser sound and treatment technique as in the active group will cover the placebo procedure.

Data collection methods

The study consists of four clinical visits (months 0, 1, 2, 3). Demographics and other baseline characteristics will be collected at the start of run-in period (month 0). Patients will complete the questionnaires mentioned (OABq, KHQ, UDI-6, PFIQ) in every visit and a three-day micturition diary a week before it. In addition, the Patient Global Impression of Improvement questionnaire (PGI-I) will be added in the last visit. Patients are advised to record twice a day their blood pressure and pulse rate, a week before the randomization and at every visit.

Primary Outcomes

The primary outcomes will be assessed by the score of the OAB-q questionnaire that consists of an eihjt-item symptom bother scale section and a 25-item health-related quality of life scale section and by the completion of a three-day voiding diary, monitoring the frequency of micturition, the urgency, and the urinary incontinence.

Secondary Outcomes

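### The repeated-measures ANOVA counts the pre-laser month-0 value as an outcome, does not say which term tests the laser, and leaves baseline adjustment to a sensitivity analysis, which gives away power

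*Protocol article*

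**What the plan says.** All places are in the protocol article.

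- **Visits** (Data collection methods): "The study consists of four clinical visits (months 0, 1, 2, 3"). The Abstract times the assessments "before each session and a month after the last one", so month 0 comes before the first laser session.
- **Power model** (Sample Size): the design has "two levels of the between-subject factor of two study groups and four levels of the within-subjects factor of time". Power is given for three terms: the time main effect, the group main effect and the interaction.
- **Longitudinal comparison** (Statistical analysis): "Repeated measurements ANOVA will be performed to evaluate the changes observed between control and intervention group over the follow-up period". No term of that ANOVA is named as the test of the laser.
- **Group comparisons** (Abstract): "Differences between groups will be assessed at baseline and every month following the three laser therapies".
- **Baseline adjustment** (Statistical analysis): "three sensitivity analyses will be performed: per-protocol analysis, robustness of trial accounting for missing data, and adjusting for baseline covariates". A separate sentence brings in mixed linear models to adjust for confounding factors. It does not mention the baseline value of the outcome.

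**The concern.** Four visits and four time levels leave no room for month 0 to be anything but one of the repeated outcomes. At month 0 no woman has had laser treatment, and randomisation makes the expected difference between arms zero. Using that value as an outcome rather than as a covariate costs power in a way that depends on which ANOVA term is read:

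- The **group main effect** averages a known zero with the three treated visits.
- The **interaction** uses month 0 as the reference, so nothing is averaged away. It still carries the full noise of the baseline measurement and spreads the effect over 3 degrees of freedom.

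The trial looks for an add-on effect over an active drug with 25 women per arm, so a missed real effect is the main risk. The baseline value that would reduce this risk is already being collected.

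**Working it through.** **Inputs from the article.** N = 50, 25 per arm; four time points; two-sided alpha 0.05; group main effect f = 0.32 and interaction f = 0.25, each with stated power 0.80.

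**Assumptions not in the article.** Outcome SD 1; equal correlation r between any two visits, taken as 0.3, 0.5 and 0.7; no effect at month 0; difference D = 0.64 SD at month 3. For two equal arms D = 2f, so f = 0.32 gives 0.64. Three patterns over months 1, 2, 3: constant (D, D, D), ramp (D/3, 2D/3, D) and late onset (0, D/2, D). Power comes from the noncentral F distribution with noncentrality λ.

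**Step 1: the article's own figures.**
- Group main effect: λ = N·4·f²/(1 + 3r) = 50·4·0.1024/2.5 = 8.19 at r = 0.5. On 1 and 48 df the power is 0.80.
- Interaction: f = 0.25 at r = 0.5 gives 0.81 with the lower-bound sphericity correction (ε = 1/3) and 0.99 without it.

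The stated 0.80 figures are therefore reproducible, under values of r and ε that the article does not give.

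**Step 2: dilution of the main effect.** A constant effect is estimated as (0 + D + D + D)/4 = 0.75D. A ramp is estimated as (0 + 1/3 + 2/3 + 1)D/4 = 0.50D, against 0.67D over months 1 to 3.

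**Step 3: power, worked at r = 0.5** (N/4 = 12.5, D² = 0.4096).
- Main effect, constant: 12.5·(0.75·0.64)²/[(1 + 3r)/4] = 12.5·0.2304/0.625 = 4.61; power 0.56.
- Interaction, 3 and 144 df: 12.5·Σ(d_j − mean d)²/(1 − r), summed over the four visits. Constant: 12.5·0.3072/0.5 = 7.68; power 0.62. Ramp: 12.5·0.2276/0.5 = 5.69; power 0.48. Late: 12.5·0.2816/0.5 = 7.04; power 0.58.
- Unadjusted month-3 t-test: 12.5·0.4096 = 5.12; power 0.60.
- Baseline-adjusted month 3: 5.12/(1 − r²) = 5.12/0.75 = 6.83; power 0.73.
- Baseline-adjusted mean of months 1 to 3, constant: 5.12/[(1 + 2r)/3 − r²] = 5.12/0.4167 = 12.29; power 0.93. The ramp multiplies λ by (2/3)², giving 5.46 and power 0.63. Late onset multiplies it by (1/2)², giving 3.07 and power 0.40.

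**Step 4: across correlations.**

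| Test | r = 0.3 | r = 0.5 | r = 0.7 |
|---|---|---|---|
| Month 3, baseline-adjusted | 0.64 | 0.73 | 0.87 |
| Month 3, unadjusted t-test | 0.60 | 0.60 | 0.60 |
| Interaction, constant | 0.47 | 0.62 | 0.85 |
| Interaction, ramp | 0.35 | 0.48 | 0.72 |
| Interaction, late onset | 0.43 | 0.58 | 0.82 |
| Group main effect, constant | 0.67 | 0.56 | 0.47 |

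The adjusted month-3 contrast is highest everywhere except for a constant effect at r = 0.3, where the group main effect reaches 0.67 against 0.64.

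**Step 5: adjustment alone, same degrees of freedom.** Part of the gain over the interaction comes from naming one contrast. To isolate the adjustment, compare the interaction with a baseline-adjusted test of months 1 to 3, also on 3 df. At 0.6 SD and r = 0.5 the powers are 0.56 and 0.78 (constant), 0.43 and 0.56 (ramp), and 0.52 and 0.59 (late onset). The adjusted test was also higher for all three patterns at r = 0.3 and 0.7.

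**The case against.** Repeated-measures ANOVA is a valid analysis and matches the design used for the power calculation. The ANOVA sentence speaks of changes between groups over time, which fits the interaction better than the main effect, and the interaction is not diluted. Mixed models are planned in their own sentence, the ANOVA is not labelled primary, and exact model terms are often left to an analysis plan that is not shown here. Much of this stands. What remains is that the article powers both terms without choosing one, and that it does assign baseline adjustment to a sensitivity analysis.

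A reader might infer four stronger things that the documents do not support:

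- **The laser effect will be diluted.** This is true only if the group main effect is the test.
- **The stated 0.80 power is wrong.** It is not. It refers to a difference averaged over all four visits; 0.56 arises only when 0.64 SD is assumed at months 1 to 3 and zero at month 0.
- **Adjustment raises power to 0.93.** That needs the full effect by month 1, after one of three sessions. With late onset at r = 0.5 the adjusted mean of months 1 to 3 has 0.40, below the interaction's 0.58.
- **Dropping women with incomplete visits will cost a known share of the sample.** A 14% loss (1 − 0.95³) follows only from an assumed 5% missing per visit. The article gives no missing rate, and it separately plans to exclude dropouts.

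**Conclusion.** The point holds as one of efficiency. Month 0 sits among the four outcomes, the test of the laser is not identified, and the more efficient use of the baseline value is placed among the sensitivity analyses. That month 0 enters the ANOVA is inferred from four visits and four time levels, since the analysis sentence itself refers only to follow-up; no other reading fits the design.

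Randomised arms have equal expected baselines, so there is no bias and no inflation of type I error. The size of the loss depends on the correlation and effect pattern, neither of which the article gives. At 0.64 SD by month 3, the adjusted month-3 contrast gains 0.04 to 0.27 over the unadjusted t-test (0.64 − 0.60 to 0.87 − 0.60). Over the interaction it gains from 0.02 (constant, r = 0.7: 0.87 − 0.85) to 0.29 (ramp, r = 0.3: 0.64 − 0.35). The exception is a constant effect at low correlation, where the main effect does slightly better. The interaction figures assume sphericity; the month-3 figures assume that the effect is present at month 3.

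**What to change.** Make the main longitudinal analysis a linear mixed model for months 1 to 3 with arm, visit, arm-by-visit, baseline value of the outcome and baseline-by-visit. Name the month-3 arm contrast in advance as the test of the laser; its power does not depend on whether the effect builds up gradually or appears late. The adjusted mean of months 1 to 3 is more powerful only if the effect is near full from month 1, so it should not be treated as interchangeable with month 3. Keep the repeated-measures ANOVA and the visit-wise tests as supportive, and state which ANOVA term is read.

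The cost is analysis wording only: no extra data or visits, and mixed models are already planned. The choice should be recorded before anyone sees unblinded results, since picking among ANOVA terms, t-tests and adjusted models afterwards would be open to selection.
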